### Recruitment

The 162 villages in Khon Kaen and 39 villages in Roi Et located within the respective ring roads are the sampling frames for each stratum. In each stratum, villages are randomly sampled based on probability proportional to population size, i.e., the population of occupied houses (the target denominator of the primary endpoint). These selected villages will be randomly allocated between the arms (see the section on Assignment of interventions below).

Villages are normally much larger than the target cluster size (10 houses); therefore, to select a starting point for the house selection, a 50 × 50 m grid and a 100-m buffer zone inside of the village perimeter will be superimposed over each village map. The buffer zone of approximately 100 m on the inside of each village border is applied to reduce potential “contamination” (in-flying mosquitoes) from neighboring villages. A random grid cell is selected in each village and 10 houses nearest the centroid of that cell selected. This procedure is followed in each village in this manner as far as practically possible. For example, if a selected household does not want to participate in the study, a neighboring house will be selected.

Informational meetings are held at the sub-district and village administrative levels to provide information about the project and benefits to the communities. Householders are visited and carefully informed about the study, and informed consent is obtained from the household head. A complete enumeration of all participants in the selected clusters will be completed with assistance from the local administration and village health volunteers (VHVs). This enumeration will be done three times during the study, allowing monitoring of potential participants’ discontinuation in the trial. Data on discontinuation, whether due to movement outside the study area or withdrawal of consent, are relevant for the secondary outcomes of DIR and MEI. Reasons for potential discontinuation will be monitored and taken into account in communication strategies to promote retention. In addition, a minor monetary compensation for those who provide blood samples for the mosquito exposure study will promote participant retention to complete follow-up of individuals.

### Interventions

Following approximately 10–12 months of baseline data collections, household interventions will begin in the selected intervention clusters (Fig. 2). The intervention specifically targets mosquito immature stages by applying a mixture of pyriproxyfen and spinosad to all permanent household containers, whether indoor or outdoor, found to contain water up to a 10-m perimeter from the house. Pyriproxyfen is an insect growth regulator (insect juvenile hormone analog) that is active against pupal stages, resulting in the inhibition of adult development (preventing emergence). It has low mammal toxicity and is recommended by WHO for vector control [52]. Spinosad is a natural insecticide produced by the soil bacterium *Saccharopolyspora spinosa*. It has a neurotoxic mode of action in insects, but with low mammal toxicity, and it is also recommended by WHO [52]. The doses recommended by WHO for *Aedes* immature mosquito control are 0.01 mg/L active ingredient (a.i.) pyriproxyfen (applied as a 0.5% granule formulation) and 0.1–0.5 mg/L a.i. spinosad (also a 0.5% granule formulation) [45, 53]. Both pyriproxyfen and spinosad have also been assessed and approved by WHO for use in drinking water containers [54, 55]. The reasons for selecting this novel intervention are that the combination of pyriproxyfen and spinosad has not yet been tested in a national dengue vector control program; that it should be effective, easy, and practical to use for national control authorities; and that its combined use reduces the risk of resistance development. The interventions will be implemented by project staff from the Ministry of Public Health, thereby ensuring adherence to intervention protocols.

**Fig. 2 Fig2:**
[figure not shown]
Time schedule of enrollment, interventions, and pre- and post-allocation data collections (based on SPIRIT 2013 figure [91])

The combination larvicide will be applied simultaneously to containers every 3 months. A buffer zone of approximately 100 m will be established around the selected intervention clusters. All selected households and other households inside this buffer zone will be treated. As far as feasibly possible, abandoned households, non-permanent households, non-occupied properties, and vacant lots inside the buffer zone will be treated in the same manner.

The households in the other half — the control arm clusters — will not receive any specific intervention initiated by the project. However, for ethical reasons, the comparator, i.e., the control arm, will receive normal governmental dengue control activities. Therefore, during the study period, both intervention and control clusters may be subjected to governmental action as part of the existing national dengue control program response. This may consist of space spraying with pyrethroids in and around a household where a dengue (index) case has been reported, including surrounding houses within a radius of 100 m from an index case. Additionally, larval control with temephos applied to household water-holding containers may occur. Larval control activities depend on the availability of staff, insecticides, and time. Although space spraying can be used in clusters of either arm (e.g., if a dengue case is detected), temephos will not be applied in the intervention clusters to avoid biased results and concerns from the public about potential negative effects on water quality. The pyriproxyfen/spinosad combination may be more effective than temephos, particularly since temephos resistance has been detected in *Ae. aegypti* in several sites in Thailand [56].

### Assignment of interventions

#### Sequence generation and implementation

The assignment of intervention (allocation) and control to clusters will be accomplished by two open public lottery events, one in each city (Fig. 2). Allocation will be done several months after and independently from cluster recruitment (Fig. 2). The lottery events will be carried out just before the first intervention. Representatives from each respective sub-district and village, including householders, district village heads, VHVs, and sub-district hospitals, will be invited to attend. Information about dengue and the purpose of the project will be provided. The reasons for randomization, its procedures, and the concepts of intervention and control will be explained. Attendants will also have a chance to ask questions about dengue, vector control, health-seeking behaviors, personal experiences of dengue, and specific details about the project.

Each of the two lotteries will be performed as follows. Small pieces of paper, of the same color and size and thus indistinguishable from one another, numbered from 1 to 18, will be folded and placed in small opaque envelopes and then placed in a bowl. Each number represents a cluster (village). A large screen with the numbered list of village names (from 1 to 18) will be shown above the bowl and visible to all. A person not involved in the study, and accepted by all participants, will be selected to make the draw. Two flip boards with large sheets of paper will be placed on either side of the bowl with the respective headings “Intervention” and “Control” (in Thai). The village on the first paper drawn will be assigned to the intervention arm, the village on the next paper drawn will be assigned to the control arm, and so on. Following the draw, the implications of being in either of the two arms will be discussed and the roles of participants, health volunteers, and sub-district hospital staff will be reviewed. By following this lottery scheme, the interventions are allocated at the same time as the sequence is generated, obviating the need for allocation concealment.

#### Blinding

This study is unblinded for both participants and data collectors because of the nature of the intervention and because it is neither practical nor financially feasible to obtain placebo (blank) granules of pyriproxyfen and spinosad to serve as a control. However, although knowledge of treatment allocation could affect mosquito endpoints (e.g., differential collection efforts), the MEI, which relies on the antibody response to *Ae. aegypti* saliva, should not be affected significantly. In terms of performance bias (i.e., systematic differences in care), dengue incidence is an endpoint, and dengue may initiate contact with health care personnel. However, the subsequent course of the episode does not affect any of the endpoints. In other words, care from health personnel will not affect the dengue diagnosis status, so performance bias should not be a concern.

### Data collection

#### Household questionnaire

Following the consent (see more details later in the paper), the household head will be asked to complete a questionnaire on the normal number of people living in the house, their age and sex, and socioeconomic status, including observations of type and quality of house structure and facilities. The household questionnaire will be repeated *annually*. However, parts of the questionnaire relating to vector control activities will be carried out *every 4 months*.

#### Disease surveillance

VHVs will carry out *weekly* visits at participating households during the 24-month study period. At each visit, household members will be asked about any fever episodes during the preceding week. Body temperature, using an axilla (under-armpit) thermometer, will be measured by the VHVs in all subjects who have reported a recent or current fever. In order to include people who have a fever at times when the VHVs are not visiting, household participants will be asked to call the VHVs by telephone to inform them about this. In that case, the VHV will attempt to visit the house immediately and collect data and temperature from that person. If that is not possible, this person will be included in the next regular VHV visit. Subjects who have or have had a fever (i.e., irrespective of body temperature at the time of the visit) will be brought on the VHV’s motorcycle or by other practical means to the collaborating sub-district hospital and offered a blood test using a commercial rapid diagnostic test kit (RDT: SD BIOLINE Dengue Duo Combo device, cat. no. 11FK46; Standard Diagnostic Inc., Suwon, Korea). This test is designed to detect dengue non-structural protein 1 (NS1) antigen and immunoglobulin M (IgM)/immunoglobulin G (IgG) antibodies. An additional 4-mL blood sample and blood spots will be taken for confirmation of DENV infection and serotype determination. All blood samples will be collected by a certified phlebotomist (or other qualified health staff) in accordance with national guidelines. All blood samples will be transferred to the Department of Microbiology, Khon Kaen University, where they will be processed for serum separation and transferred to a –80 °C freezer to await further processing. RNA extraction will be performed using a QIAamp® Viral RNA Mini Kit (Qiagen, Hilden, Germany) on serum samples. Extracted RNA will be stored at –80 °C for viral detection and sequencing. DENV will be confirmed by nucleic acid detection using reverse transcription polymerase chain reaction (RT-PCR) with DN-F and DN-R primers as described in Shu et al. [57]. Data on potential risk factors, such as patient’s age, travel history, and previous dengue infection history, will be collected at time of blood sampling. Although not part of the outcome factors, tests for Zika [58] and chikungunya [59] infections will be performed using RT-PCR and sequencing for confirmation.

##### Inclusion criteria for individuals

The inclusion criteria for individuals are as follows:Self-reported fever within the last 7 daysAge ≥ 1 year old

##### Exclusion criteria for individuals

The exclusion criteria for individuals are as follows:A continuous travel history outside the district during the last 7 daysDiseases, such as HIV/AIDS or other health conditions, that preclude participation in the study, based on self-evaluationApparent inability to give informed consent, e.g., due to mental disability or other incapacity, or lack of a legally authorized representative

#### Exposure to mosquito bites

To assess the level of exposure to *Aedes* bites, blood spots on filter paper will be taken from each person designated as a fever case (detected during the weekly visits) for immunological analysis. In addition, recurring blood spot collections will be taken from two additional individuals, ideally the same adult and child (5–14 years old) each time. These collections will be done *monthly* in each of three households per cluster and *every 4 months* in all households per cluster. Individuals will be selected based on their availability and willingness to participate over the full course of the study; ideally, they will be individuals who are present at home most of the time. Participants providing blood spots will receive a minor monetary compensation. As the immune background will be variable between individuals, the same individuals are needed to follow changes in their immune response to *Aedes* bites over time. Blood samples will be taken from people in their households by a certified phlebotomist (or other qualified health staff) using a finger prick. Two blood spots (2 × 75 μL) will be placed on filter paper (Protein Card Saver 903™) and stored at 4 °C until further analyses.

Blood samples will be eluted in phosphate-buffered saline (PBS) with 0.1% Tween for 24 h at 4 °C and then stored at –20 °C. The salivary peptide Nterm-34 kDa (Genepep, St Clement de Rivière, France) will be used as an *Aedes*-specific biomarker to quantify the immune response to *Ae. aegypti* mosquito bites by immunoassays [60]. Briefly, the peptide will be coated on a certified plate (MAXISORP®; Nunc, Roskilde, Denmark), and the blood samples will be incubated overnight at 4 °C to allow specific IgG to bind to the salivary peptide. An anti-human IgG secondary antibody enzyme conjugate will be incubated to bind individual IgG attached to the biomarker. Substrate will be added for color development. The level of immune response will be assessed by measuring the absorbance after 120 min at 405 nm (Sunrise™ spectrophotometer, Tecan, Männedorf, Switzerland). Each sample will be compared in duplicate wells and in a blank well (without antigen) to measure non-specific reactions. Individual results will be expressed as a differential optical density (ΔOD) value calculated as ΔOD = OD_x_ − OD_n_, where OD_x_ represents the mean of individual OD values in the two wells containing antigen, and ODn represents the OD value in the well without antigen. Specific anti-Nterm-34 kDa IgG response will be assayed in individuals who have not been exposed to *Ae. aegypti* mosquitoes to quantify the non-specific background antibody level and to calculate the specific immune threshold (TR) as follows:$$ \mathrm{TR}=\mathrm{mean}\;\left({\Delta \mathrm{OD}}_{\mathrm{unexposed}}\right)+3\mathrm{SD}. $$

The main outcome for this immune response assay will be ΔOD, which is a continuous variable. In addition, a binary outcome will be calculated by considering an individual to be “exposed” if the ΔOD value is higher than the TR calculated from unexposed individuals.

#### Entomological collections

Mosquito collections will be carried out in all participating households *every 4 months* (Fig. 2). In addition, *monthly* collections will be done in the three sentinel households per cluster, using the same households as those used for the blood spot collections for logistical reasons. The following data will be recorded from each household: number of total containers (potential breeding sites, wet or dry), number of containers with water, number of mosquito positive and negative containers (any species), container type, and location (indoors/outdoors) using defined criteria. Mosquito larvae will be collected from all positive containers using a standard larval dipper to determine species composition (both *Ae. aegypti* and *Ae. albopictus* will be identified and recorded). Pupae will be collected using the pupal/demographic survey method [19] and the “five-sweep” net procedure for very large containers [61].

Adult mosquitoes will be collected for 15 min indoors (in living rooms, bedrooms, etc.) and 15 min outdoors (among man-made articles, vegetation, etc.) from each household using a Prokopack mechanical aspirator [62]. Adult mosquitoes will also be collected using stationary sticky lure gravid *Aedes* traps [63] placed in a location where mosquitoes are abundant (based on householders’ knowledge) at four selected households for *7 consecutive days every month*. Specimens will be taken to a laboratory for sorting and identification using a stereomicroscope and morphological keys [64, 65]. Larvae (separated by species) and pupae (separated by species and sex) will be stored in absolute 99.5% ethanol in labeled 1.5-mL Eppendorf® tubes. Blood digestion status (fed or not fed) of female mosquitoes will be determined by external examination of abdomens. Adult mosquitoes (separated by species and sex) will be stored individually in absolute 99.5% ethanol in 1.5-mL labeled Eppendorf tubes. All specimens will be transported to Khon Kaen University and stored at –80 °C until further processing.

#### Virus detection in mosquitoes

Virus detection will be performed on adults and pupae of *Ae. aegypti* and *Ae. albopictus*. The heads and abdomens of adult mosquitoes will be stored separately. Abdomens will be pooled using a pool size of 5–10 individual abdomens depending on abundance. Virus detection will first be performed on all pools; then, if positive, serotype detection will be done on individual mosquitoes (heads). As heads and abdomens cannot be separated in pupae, virus and serotype detection will be done on pools of whole bodies of pupae. The prevalence of infection in the pupal population, based on the proportion of positive pools, will be estimated using previously described methods [66, 67]. The total RNA will be isolated from mosquito specimens using Favorgen® reagent (FavorPrep^TM^ Tissue Total RNA Mini Kit) following manufacturer instructions. The final solution will be stored at –80 °C. DENV presence will be confirmed by real-time quantitative RT-PCR (qRT-PCR) conducted in the LightCycler® 480 Real-Time qPCR System using KAPA SYBR® FAST qPCR Master Mix (2X) Universal [68]. The Master Mix contains an optimized MgCl_2_ concentration. Positive samples will be submitted to a second specific qPCR to determine the DENV serotype [69, 70].

#### Climate data

Climate data, including daily temperature, rainfall, and humidity data, will be collected from permanent weather stations located in Khon Kaen and Roi Et (Department of Meteorology of Thailand). Additionally, four rainfall gauges (three manual and one automatic) and eight temperature-humidity data loggers (iButtons Hygrochron Loggers, DS1923-F5) will be placed in each city at suitable locations to capture local variations.

### Data management

Each participating household will be given a 6-digit identification number (indicating province, village, and household number) and an identification plate (with project name and ID number) attached in a secure location to the house. Each household member will also receive a unique ID number. Data from household questionnaires at household enrollment, entomological collections, blood spot sampling at households and hospitals (venipuncture for dengue positivity confirmation), and disease surveillance data by VHVs will be collected on paper forms. Data will be securely stored in a password-protected central database. All hardcopy and electronic data will be placed in locked spaces or password-protected computers. Data management procedures will be detailed in specific standard operating procedures and can be requested from the corresponding author.

### Analysis

#### Index calculations

For all outcomes, baseline measurements will start in the second half of 2017. Post-intervention measurements will start in the second half of 2018. The following indices or rates will be used:*Adult index (AI)*. Number of adult female *Ae. aegypti* and *Ae. albopictus* per house (combined species) collected both indoors and outdoors for 15 min at each location (30 min total collection time), using a battery-driven mechanical aspirator. Collections will occur once every 4 months in all households and once every month in three repeat sentinel households per cluster*Dengue incidence rate (DIR)*. Number of confirmed dengue cases divided by observation days of household populations. All household members with a fever will be identified during weekly VHV visits in participating households. Confirmed dengue cases are those febrile patients with a rapid diagnostic test (RDT) positive for NS1, IgM, IgG, or combinations thereof and a subsequent positive laboratory RT-PCR*Mosquito exposure index (MEI)*. ΔOD in IgG antibodies to *Ae. aegypti* Nterm-34 kDa salivary peptide using immunoassays, within the sampling scheme described above. Also the proportion for whom this differential optical density is above the TR defined above*Infected adult index (IAI)*. Number of DENV-infected adult female *Ae. aegypti* and *Ae. albopictus* per house (combined species) collected both indoors and outdoors for 15 min each, using a battery-driven mechanical aspirator. DENV presence will be confirmed by real-time RT-PCR as described above*Adult sticky trap index (ASTI)*. Number of adult female *Ae. aegypti* and *Ae. albopictus* (combined species) collected each month using one sticky trap per house baited with an oviposition attractant hay infusion. Collections will be done in three selected households for 7 consecutive days per month*Pupae per person index (PPI)*. Total number of *Aedes* pupae collected in participating households divided by the number of persons in that household. Collections will be done once every 4 months in all households and once every month in three repeat sentinel households per cluster*Breteau index (BI)*. Number of immature *Aedes* positive containers per 100 houses measured at the cluster level. Collections will be done once every 4 months in all households and once every month in three repeat sentinel households per cluster

Other indices are described in Table 1.

#### Analysis populations

At the cluster level, analysis will be by intention to treat, i.e., taking the trial arm as that to which each cluster was randomized. At the individual level, people will be taken to have the allocation of the arm in which they are resident at the time of any data contributed. There will be no intention-to-treat analysis, unless, for unforeseen reasons, the Technical Advisory Committee recommends that one be done. A flowchart showing numbers of clusters and average numbers of households per cluster over time will be constructed in accordance with Consolidated Standards of Reporting Trials (CONSORT) guidelines [71]. For the primary analysis, missing data may occur if complete clusters decline to continue in the trial. In this case, the cluster will still be included as long as any data on the primary outcome are available. This does introduce a risk of bias in estimating effectiveness, if loss of clusters is related to performance of the interventions.

#### Statistical methods

For the entomological endpoints, clustering will be taken into account by analyzing summary measures at the level of cluster. The MEI, expressed as a continuous variable, is a characteristic of individual people, not houses, and its main analysis will be by multivariable multilevel modeling with three levels: cluster, individuals within clusters, and measurements (time points) within individuals. As before, the exposure of main interest will be the arm of the trial (intervention versus control). Individual-level covariates will include age (5–14, 15–25, and > 25 years) and sex. Vector control intervention (i.e., arm of the trial) will be used as a covariate at cluster level. Other cluster-level covariates may include abiotic factors (such as rainfall, temperature, and relative humidity) and population density. An additional analysis of MEI will be by summary measures, as for the other endpoints.

For all analyses of summary measures, the arm of the trial will be the exposure of main interest and will be included in regression models as a dichotomous variable. Stratification will be represented by including a dichotomous variable for city. Finally, the baseline value of each outcome, summarized over the pre-intervention rounds, will be included as a categorical variable, with the expectation that this will reduce the residual error.

For each outcome variable, the response variable for the main analysis will be the aggregate value, for each cluster, of the post-baseline measurements. However, for the primary endpoint (AI), an additional analysis will include the values at each post-baseline time point for each cluster, and will include an interaction between the arm of the trial and the time point, with the aim of identifying a possibly waning effect of the interventions.

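### The main model for the mosquito exposure index names neither city nor baseline level, and a later general sentence gives the same endpoint a different main analysis

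*Protocol article*

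**What the plan says.** All the analysis text is in the Statistical methods section of the protocol article.

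- **Main MEI model.** For the continuous MEI, "its main analysis will be by multivariable multilevel modeling with three levels: cluster, individuals within clusters, and measurements (time points) within individuals". Its covariates are then listed. "Individual-level covariates will include age (5–14, 15–25, and > 25 years) and sex"; trial arm enters at cluster level; and "Other cluster-level covariates may include abiotic factors (such as rainfall, temperature, and relative humidity) and population density". Summary measures are described as an additional MEI analysis.
- **Summary-measure analyses.** The next paragraph opens "For all analyses of summary measures, the arm of the trial will be the exposure of main interest". Within that paragraph, "Stratification will be represented by including a dichotomous variable for city", and "the baseline value of each outcome, summarized over the pre-intervention rounds, will be included as a categorical variable", with the stated expectation of less residual error.
- **General rule.** The paragraph after that says that, for each outcome variable, "the response variable for the main analysis will be the aggregate value, for each cluster, of the post-baseline measurements". The only qualification that follows concerns a further analysis of the adult index.

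Three other sections bear on the point. Trial design gives lower residual error as a reason for stratifying by city. Exposure to mosquito bites explains the repeated sampling: "As the immune background will be variable between individuals, the same individuals are needed to follow changes in their immune response". Blinding presents the MEI as an outcome that knowledge of allocation should not much affect, unlike the mosquito collections.

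**The concern.** The two covariates that the protocol itself expects to sharpen the arm comparison are attached to the additional MEI analysis and not to the main one. Baseline ΔOD is already being collected in the same people, precisely because background differs between them, yet the main model as printed makes no stated use of it.

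The general rule also cannot hold alongside the three-level model. A single aggregate per cluster cannot be the response in a model of repeated measurements within individuals. Read literally, the MEI has two main analyses, and the choice could be made after results are seen.

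The MEI is secondary, but it is the outcome the protocol sets against possible collector bias in the unblinded mosquito counts. An imprecise MEI estimate could wrongly appear not to support a real effect on mosquitoes.

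**Working it through.** **Plan's own figure.** There is none to reproduce. The Sample size section concerns the adult index only; the document gives no variance, intracluster correlation, power or baseline/follow-up correlation for the MEI. The sizes below are therefore ranges on stated assumptions.

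**Step 1: the text side by side.**

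| Item | MEI three-level main model | Summary-measure analyses (additional for MEI) |
|---|---|---|
| Response | measurements within individuals | one aggregate per cluster |
| Age, sex | named | not named |
| City | not named | named |
| Baseline value | not named | named |
| Period of the response | not stated for this model | post-baseline |

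**Step 2: is there bias?** The Sample size section fixes 9 clusters per arm in each of two cities, 36 in all. City is balanced by design and baseline precedes allocation, so omitting either leaves the arm contrast unbiased in a post-intervention model. The cost is precision.

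**Step 3: precision from baseline.** Arm is assigned to clusters, so the relevant r is the correlation between baseline and follow-up *cluster means*. With baseline as a linear term,

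Var(adjusted) / Var(unadjusted) = 1 − r².

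To put this on a power scale, suppose the adjusted analysis had 90% power at two-sided 0.05 (an assumption, not a plan figure for the MEI). Effect/SE is then 1.960 + 1.282 = 3.242. Without adjustment it is 3.242 × √(1 − r²), and power is Φ of that minus 1.960.

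| Assumed r | Variance reduction r² | Unadjusted effect/SE | Unadjusted power |
|---|---|---|---|
| 0.3 | 9% | 3.09 | 87% |
| 0.5 | 25% | 2.81 | 80% |
| 0.7 | 49% | 2.31 | 64% |

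**Step 4: precision from city.** If city explains a share R² of the variance between cluster means, the same formula applies with R² in place of r². For assumed shares of 5% and 30%, 90% power with city becomes 88% and 77% without it. This does not add to step 3, because a baseline cluster mean already carries part of any city difference.

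**Step 5: the conditional case.** Suppose baseline-year samples did enter under one constant arm term. Arm does not change within a cluster, so with balanced data its coefficient is the difference between cluster means over all rounds, and random intercepts do not alter that. The Abstract gives 2 years of collection; the Interventions section gives about 10–12 months of baseline. With even sampling over time and a constant effect from the first treatment, the coefficient estimates:

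- 12-month baseline: 12/24 = 50% of the true effect
- 10-month baseline: 14/24 = 58% of the true effect

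As a check, 150 balanced trials were simulated (36 clusters, 20 people each, 3 rounds before and 3 after; assumed true effect −0.30). The mean estimate was −0.14 with all rounds under one arm term, −0.29 post-only unadjusted, and −0.29 post-only with city and baseline. This agrees with steps 2 and 5.

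**The case against.** The best case for the plan has four parts.

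1. **The lists are open.** They say what covariates will or may be included and exclude nothing; a full analysis plan could add city and baseline. This stands in part. The text does not forbid adjustment, but it also does not merely stay silent: it gives the MEI model its own list and ties city and baseline to another class of analysis.
2. **The specific rule governs the general one.** The MEI sentence explains why this outcome is treated differently, and the aggregate sentence follows directly on the paragraph about summary measures. That is the natural reading, so this part is a drafting fix. The rule still says each outcome, without exception.
3. **The correlation is unknown.** The Discussion expects the IgG response to last no more than 15–30 days, which makes a strong year-to-year correlation uncertain. This stands, and is why r = 0.3, with a 9% gain, belongs in the range.
4. **Adjustment is already planned.** The additional MEI analysis includes city and baseline, and the primary outcome is unaffected. Both are true; they limit the weight of the point.

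A reader might go further and infer that the planned MEI effect will be diluted by about half. The document does not support that. It nowhere says that baseline samples enter under one arm term, and its only sentence on the window for main-analysis responses says post-baseline. If that sentence governs the MEI, there is no dilution; if it does not, the conflict between the two rules goes away but the window is left open.

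**Conclusion.** The point holds as a matter of precision and clarity, for a secondary outcome. As printed, city and baseline adjustment are specified for the additional MEI analysis and not for the main one, against the protocol's own reasons for collecting and using them. The general aggregate sentence conflicts with the MEI model.

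The loss is one of variance, not validity: about r² from omitting baseline, or 9%, 25% and 49% at assumed cluster-mean correlations of 0.3, 0.5 and 0.7. No single value in that range can be attributed to this trial.

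Shrinkage to about 50–58% of the true effect would arise only under pooling with a single arm term, which is neither stated nor excluded for this model. It is an alternative to the precision loss in step 3 of the working, not a further harm on top of it. A reader might also take the omission of city to bias the comparison; the fixed 9-and-9 allocation within each city rules that out.

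This should be corrected before the MEI analysis is run, but it does not touch the primary analysis.

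**What to change.** Make two changes of wording in the Statistical methods section.

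1. Define the MEI main model in one of two ways:
   - post-intervention measurements only, with city and pre-intervention ΔOD as covariates, using the individual's mean, or the cluster baseline mean where the individual has none; or
   - all measurements, with city and an arm-by-period term, that term being the estimand.
2. Limit the sentence on post-baseline cluster aggregates to the outcomes whose main analysis is by summary measures.

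The cost is drafting only. City is known for every cluster and baseline ΔOD is already scheduled for collection, so no new data, visits or clusters are needed.
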